**Table 4 Tab4:** **Visit schedule, arm 2**

	Screening	Week 0	Week 24	Week 28	Week 32	Week 36	Week 40	Week 44	Week 48 (final visit)
Visit number	V1	V2	V3	V4	V5	V6	V7	V8	V9
Consent form	X								
Medical history	X								
Dietary survey		X							
Physical exam and vital signs	X	X	X	X	X	X	X	X	X
Adverse events		X	X	X	X	X	X	X	X
Hematology	X	X	X	X	X	X	X	X	X
Chemistry	X	X	X	X	X	X	X	X	X
Pregnancy test (women only)	X		X						
Hepatitis B and C tests	X								
ART review	X								
Syphilis test^1^	X		X						X
T-cell activation and inflammatory markers		X	X						X
HIV viral load^2^	X		X			X			X
Levels of tryptophan, niacin and its derivatives		X	X		X		X		X
ER niacin admin^3^				X	X	X	X	X	X
Bays-Ballantyne questionnaire				X	X	X	X	X	X
WHOQOL-HIV BREF, CES-D, POMS, HVLT-R™, and CANTAB™ tests^4^		X	X						X
SMAQ^5^		X	X			X			X

^1^If syphilis test is positive at screening, participants will be retested at weeks 24 and 48.

^2^HIV viral load testing will be performed as indicated by treating physician.

^3^Participants will start ER niacin administration after their week 24 visit.

^4^Neurocognitive assessments are optional; WHOQOL-HIV BREF, World Health Organization quality of life instrument in patients with HIV infection-brief; CES-D, Center for Epidemiologic Studies Depression Scale; POMS, Profile of Mood State; HVLT-R™, Hopkins Verbal Learning Test Revised; CANTAB, Cambridge Neuropsychological Test Automated Battery.

^5^SMAQ, Simple Medication Adherence Questionnaire.

### Measurements

At baseline, the following clinical information will be collected for all participants: age, education, ethnicity, handedness, communication skills (able to communicate in English and/or French adequately, first language), list of current psychoactive medication, dosage and date of treatment initiation, psychiatric disorders, duration of HIV infection, current ART regimen (duration in months), review of ART history, CD4+ T-cell count within the past three months, nadir CD4+ T-cell count, HIV plasma viral load within the past three months and any preexisting medical conditions, signs, or symptoms.

### Clinical parameters

Assessments performed at scheduled study visits will monitor safety (physical exam with vital signs, occurrence of adverse events (AEs and concomitant medications) and will determine the dermatological effects of flushing. At the follow-up visits, some or all of the following assessments will be done: plasma HIV RNA levels, hematology, fasted biochemistry, CD4+ T-cell and CD8+ T-cell counts, plasma levels of Trp and Kyn, T-cell activation and inflammatory markers and testing for syphilis if the participant tested positive at baseline (week 0).

### Dietary survey

A dietary survey to determine the pre-study dietary niacin levels for each participant will be completed at week 0 (baseline). This survey will be performed by an MUHC dietician with expertise in HIV patient management. Participants will be instructed to keep their diet constant during the study.

### Laboratory investigations

#### Medication adherence

Adherence for both ER niacin and ART will be measured using the Simple Medication Adherence Questionnaire (SMAQ) [45]. This questionnaire consists of seven binary questions regarding adherence during the three previous months. The SMAQ score ranges from 0 to 7, with 0 corresponding to 100% adherence.

### Optional neurocognitive assessments: quality of life, depression and neurocognitive scores

QoL will be assessed with the World Health Organization quality of life instrument in patients with HIV infection brief (WHOQOL-HIV BREF) [46], an instrument that provides a reliable and valid assessment of wellbeing in people living with HIV and AIDS. This 31-item assessment has very good discriminant validity with reference to ‘known’ disease groups, and generally very good internal consistency reliability.

Mood will be assessed by the Center for Epidemiologic Studies Depression scale (CES-D), and the Profile of Mood State (POMS) questionnaire. The CES-D is a 20-item short self-report scale designed to measure depressive symptomatology in the general population [47]. It has very high internal consistency and adequate test-retest repeatability. The POMS will measure depression as well as other mood states, irritability in particular. It is composed of six scales: agreeable-hostile, composed-anxious, elated-depressed, confident-unsure, energetic-tired and clearheaded-confused. It is highly sensitive to non-clinical changes in mood states [48].

Changes in cognition will be assessed with the Hopkins Verbal Learning Test Revised (HVLT-R™) and the Cambridge Neuropsychological Test Automated Battery (CANTAB™). The HVLT-R is a pencil and paper test that explores verbal episodic memory, learning, recall and verbal recognition processes [49]. The CANTAB is a computer-based cognitive assessment system; the computerized tests do not present any limitations due to language [50]. Eight subtests have been selected as representing the cognitive domains which are more at risk of decline in HIV infection: motor screening, rapid visual information processing, spatial working memory, paired associate learning, big/little circle, intra-extra dimensional set shift, stop signal task and Stockings of Cambridge task. The neuropsychological tests will be performed at weeks 0, 24 and 48 only on participants who consent to the optional neurocognitive evaluation. The entire testing battery will be administered by a trained research assistant under the supervision of a neuropsychologist. The total assessment time (including tests and questionnaires) will be approximately two hours and 30 minutes per session.

### Research hypothesis

The main hypothesis to be tested in this study is that ER niacin co-administration with ART will be associated with decreased immunosuppressive Trp catabolism and T-cell activation as determined by the proportion of activated CD8+ CD38+ HLA-DR+ T-cells.

### Study outcome measures

The primary objective of this study will be to assess the impact of ER niacin supplementation in combination with ART compared to ART alone on T-cell immune activation as defined by changes in the percentage of CD8+ CD38+ HLA-DR+ T-cells.

The secondary objectives of this study will be to: 1) assess the change in total CD4+ T-cell count after ER niacin administration; 2) explore the effect of ER niacin on Th17 and Treg cell frequencies in blood; 3) explore the effect of ER niacin on cytokines and inflammatory markers such as interferon-alpha (IFN-α), IL-1, IL-6 and IL-17, interferon gamma-induced protein 10 (IP-10), D-dimers, highly-sensitive C-reactive protein (hsCRP) and LPS; 4) assess the influence of ER niacin on Trp plasma levels; 5) assess changes in cholesterol and triglyceride levels; 6) evaluate the impact of ER niacin on QoL, fatigue, depression and neurocognitive scores; and 7) explore ER niacin tolerance.

### Efficacy variables

#### T-cell activation assessments

The primary endpoint of this study will be changes in the percentage of CD8+ CD38+ HLA-DR+ T-cells which will be used as a marker for the change in the level of T-cell activation. Enumeration of the CD38 activation marker on total CD4+ and CD8+ T-cells, as well as on naïve, memory and effector cell subsets, will be performed by eight-color flow cytometry. This will allow for the precise identification of which cell subpopulation(s) is or are more likely to downregulate CD38 expression following ER niacin administration.

The absolute numbers of activated T-cell subsets will be computed using: 1) the white blood cell (WBC) count; 2) the percentage of lymphocytes; 3) the percentage of CD4+ and CD8+ T-cells; and 4) the percentage of each CD4+ or CD8+ T-cell subset (naïve, central memory, pre-terminal effector memory or terminal effector memory).

#### T-cell activation in blood

Levels of T-cell activation will be assessed in blood samples on weeks 0, 24 and 48. This analysis will be performed using specific monoclonal antibodies (mAbs) as previously reported [51, 52]. Briefly, peripheral blood mononuclear cells (PBMCs) will be obtained by Ficoll-Hypaque density gradient centrifugation. The PBMCs will be either stained with the appropriate mAbs or stored in liquid nitrogen until used. T-cell subsets will be identified using a mAb cocktail specific for CD3, CD4, CD8, CD45RA, CCR7, CD27, CD38 and HLA-DR. One million PBMCs will be incubated in a 96-well polystyrene plate (Fisher Scientific, Ottawa, Ontario, Canada) in the dark at 4°C for 30 minutes. The cells will be washed twice with phosphate buffer saline (Fisher Scientific, Ottawa, Ontario, Canada) containing 1% fetal calf serum (Sigma Aldrich, Oakville, Ontario, Canada), resuspended in 250 μL 2% paraformaldehyde (Sigma Aldrich, Oakville, Ontario, Canada) and stored at 4°C for up to 12 hours before flow cytometric analysis of cell surface expression. Unstained cells and fluorescence minus one mAbs will be used as controls in all experiments. Lymphocytes will be identified first according to their light-scattering properties and then analysed for expression of lymphocyte markers. CD4+ and CD8+ T-cells will be defined as CD3+ CD4+ CD8- T-cells and CD3+ CD4- CD8+ T-cells, respectively. The associated expressions of CD45RA, CCR7 and CD27 will be then used to obtain the percentages of cells distinctively identifying naïve (CD45RA+ CCR7+ CD27+), central memory (CD45RA- CCR7+ CD27+), pre-terminal effector memory (CD45RA- CCR7- CD27-) and terminal effector memory (CD45RA+ CCR7- CD27-) CD4+ and CD8+ T-cell subsets. The expression of the CD38 activation marker will be then determined for each CD4+ or CD8+ T-cell subset. FlowJo data analysis software (FlowJo, LLC, Ashland, Oregon, United States) will be used for data analysis.

#### Th17 and Treg cell assessments

PBMCs will be cultured in 48-well culture plates at 0.5 to 1 × 10^6^ cells/mL per well and will be stimulated with 5 ng/mL phorbol 12-myristate 13-acetate (PMA) and 1 μg/ml ionomycin (both from Sigma Aldrich, Oakville, Ontario, Canada) for two hours at 37°C. A total of 2 μg/ml brefeldin A (Sigma Aldrich, Oakville, Ontario, Canada) will then be added to block cytokine secretion and cells will be cultured for 18 hours at 37°C. PBMCs will be surface stained followed by fixation and permeabilization using the Cytofix/Cytoperm Permeabilization kit (BD Bioscience, Mississauga, Ontario, Canada) for intracellular staining for IL-17A and IFN-ɣ (positive control). Treg cells will be defined by flow cytometry as being CD3+ CD4+ CD25^high^ CD127^low^ FoxP3^high^ and Th17 cells as being CD3+ CD4+ IL-17A+ upon PMA and ionomycin stimulation [27].

### Monocyte and dendritic cell immune activation

As IDO enzyme is expressed by monocytes and dendritic cells, we will also assess the impact of ER niacin on the activation of monocytes and dendritic cells (DCs). The expression of the activation markers CD69 and HLA-DR on CD14+ monocytes, as well as the expression of CD86 and CD83, markers of DC activation and maturation on both CD11c+ myeloid DCs and CD123+ plasmacytoid DC, will be evaluated by flow cytometry.

#### Inflammatory markers assessments

Although inflammatory markers such as D-dimer and hsCRP are related to cardiovascular non-AIDS events during HIV infection, it has become clear that HIV induces a hypercoagulable state as a consequence of impaired endothelial function despite ART. The effect of ER niacin on the levels of IFN-α, IL-1, IL-6, IL-17, IP-10, D-dimer and hsCRP, as well as on the microbial translocation markers sCD14 and LPS, will be assessed by Enzyme-Linked Immunosorbent Assay ELISA [51].

### Plasma Trp and Kyn assessments

Plasma levels of Trp and Kyn will be measured by an automated on-line solid-phase extraction-liquid chromatographic-tandem mass spectrometric (XLC-MS/MS) method as previously described [27, 53].

### Sample size and statistical analyses

Because this proof-of-concept study will explore a phenomenon with little *in vivo* data, a convenience sample of 20 participants was chosen without formal power calculations. The data that will be obtained should be sufficient to assist in such calculations for future large studies.

The primary comparison is the change in the percentage of CD3+ CD8+ HLA-DR+ T-cells between the period of ER niacin plus ART (from week 0 to week 24 of arm 1, and from week 24 to week 48 of arm 2) and the control periods of ART alone (from week 24 to 48 of arm 1, and from week 0 to 24 of arm 2). If the treatment effects in the two time periods look distinctly dissimilar, which may occur due to carryover effects of treatment, we will focus on the comparison between arms 1 and 2 at the end of 24 weeks.

In each time period, a between-groups t-test will be used to compare the change in the percentage of CD3+ CD8+ HLA-DR+ T-cells during the ER niacin plus ART treatment with the change in the percentage of CD3+ CD8+ HLA-DR+ T-cells in the ART treatment alone. If the results of these comparisons in the two treatment periods are similar, then within each treatment order, a paired t-test will be used to compare the change in the percentage of CD3+ CD8+ HLA-DR+ T-cells during the ER niacin plus ART period with the change in the percentage of CD8+ CD38+ T-cells during the ART-alone period and the results of these two comparisons will be combined to generate a pooled estimate of the treatment effect. The same analytic approach will be used for the secondary outcomes. The primary comparison would be based on 20 pairs of observations, with each subject receiving active ER niacin compared to the control time-points (ART alone without ER niacin) in different time-points. The ratio of the difference between the study groups to the standard deviation of the differences would have to be fairly large (0.625) to achieve a power of 80%. All statistical tests performed will be two-tailed with significance determined by reference to the 5% level, unless otherwise stated.

The same analytic approach will be used for the secondary outcomes as for the primary outcome. The secondary outcomes are: the change in total CD4+ T-cell count, changes in Th17 cells and Treg cells in blood and gut mucosa samples (from substudy), changes in cytokines and in inflammatory markers such as IFN-α, IL-1, IL-6, IL-17, IP-10, D-dimers, hsCRP, sCD14 and LPS, the change in Trp plasma levels, changes in monocyte and dendritic cell immune activation, changes in cholesterol and triglycerides and changes in QoL, fatigue, depression and neurocognitive scores, using computerized and pencil and paper tests (from optional procedures).

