This pilot crossover study will be conducted to examine the ability of ER niacin to reduce immune activation, which may in turn increase CD4 recovery in HIV-infected individuals with suboptimal immune responses despite sustained virologic suppression. The main hypothesis to be tested is that ER niacin co-administration with ART will be associated with decreased T-cell activation as determined by changes in the percentage of activated CD8+ CD38+ HLA-DR+ T-cells. If so, during administration of ER niacin, participants should experience a time-dependent decrease in T-cell activation, and such a decrease may reverse after ER niacin is discontinued. We will also examine the effects of ER niacin on cognition. To this end, we will assess the neurocognitive function and QoL in participants using standardized neuropsychological (NP) tests and questionnaires.

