**Figure 1 Fig1:**
[figure not shown]
**Study design.** Arm 1: ER niacin administration begins at week 0 and ends at week 24 (defined as ‘immediate use’ arm). Arm 2: ER niacin administration begins after the week 24 visit and ends at week 48 (defined as ‘deferred use’ arm). ART, Antiretroviral therapy; ER, extended-release.

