### Randomization

Once a participant is deemed eligible and has provided consent, they will be randomized to one of two treatment arms in a 1:1 ratio to receive the immediate or the deferred intervention with ER niacin. Prior to the initiation of the trial, a CTN staff member not directly associated with the implementation of the trial will use an SAS module (SAS Institute, Cary, North Carolina, United States) to generate sequential participant study identification numbers which will be loaded onto a webpage randomization system. The treatment groups will be: arm 1: ER niacin supplementation for 24 weeks followed by 24 weeks of ART alone, and arm 2: 24 weeks of ART alone followed by ER niacin supplementation for 24 weeks. When a participant is deemed eligible, the study coordinator signs onto the password-protected randomization webpage which issues the allocation. A transaction file records the study identification number, allocation and date and time of randomization.

Scheduled visits for arm 1 of this study will be screening (up to four weeks prior to treatment), week 0 (baseline), week 4, week 8, week 12, week 16, week 20, week 24, and week 48/final visit (or other if terminating early). Table 3 shows the arm 1 schedule of study events.

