**Table 3 Tab3:** **Visit schedule, arm 1**

	Screening	Week 0	Week 4	Week 8	Week 12	Week 16	Week 20	Week 24	Week 48 (final visit)
Visit number	V1	V2	V3	V4	V5	V6	V7	V8	V9
Consent form	X								
Medical history	X								
Dietary survey		X							
Physical exam and vital signs	X	X	X	X	X	X	X	X	X
Adverse events		X	X	X	X	X	X	X	X
Hematology	X	X	X	X	X	X	X	X	X
Chemistry	X	X	X	X	X	X	X	X	X
Pregnancy test (women only)	X								
Hepatitis B and C tests	X								
ART review	X								
Syphilis test^1^	X							X	X
T-cell activation and inflammatory markers		X						X	X
HIV viral load^2^	X				X			X	X
Levels of tryptophan, niacin and its derivatives		X		X		X		X	X
ER niacin admin^3^		X	X	X	X	X	X	X	
Bays-Ballantyne questionnaire			X	X	X	X	X	X	
WHOQOL-HIV BREF, CES-D, POMS, HVLT-R™, and CANTAB™ tests^4^		X						X	X
SMAQ^5^		X			X			X	X

^1^If Syphilis test is positive at screening, participants will be retested at weeks 24 and 48.

^2^HIV viral load testing will be performed as indicated by treating physician.

^3^Participants will end ER niacin administration at the end of week 24.

^4^Neurocognitive assessments are optional; WHOQOL-HIV BREF, World Health Organization quality of life instrument in patients with HIV infection-brief; CES-D, Center for Epidemiologic Studies Depression Scale; POMS, Profile of Mood State; HVLT-R™, Hopkins Verbal Learning Test Revised; CANTAB, Cambridge Neuropsychological Test Automated Battery.

^5^SMAQ, Simple Medication Adherence Questionnaire.

Scheduled visits for arm 2 of this study will be screening (up to four weeks prior to study enrolment), week 0 (baseline), week 24, week 28, week 32, week 36, week 40, week 44 and week 48/final visit (or other if terminating early). Table 4 shows the arm 2 schedule of study events.

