Another objective of this study is to examine Niaspan FCT tolerance. Flushing at the initiation of niacin therapy is the most commonly reported side effect and is defined as redness, warmth, itching and/or a tingling sensation on the face, neck, chest and back [55]. This is a natural reaction signalling that niacin is in the bloodstream. Flushing is believed to be caused by an increase in blood flow and by the expansion of blood vessels close to the surface of the skin. Most participants on Niaspan FCT will experience this sensation, usually at the start of therapy or when the dosing is increased (occurring in up to 88% of participants in previous studies). These effects are usually transient and rarely require discontinuation of therapy (fewer than 6% discontinued due to flushing) [44]. Niaspan FCT, the drug to be administered in this pilot study, is an ER form of niacin that is dosed once each night when cholesterol synthesis and fatty acid mobilization are at their peak [38]. This form of niacin has intermediate-release characteristics and is thus designed to minimize both liver enzyme elevation and flushing. It is expected that for most participants, the flushing in response to ER niacin will occur over the first eight weeks of therapy and should become milder and less frequent as their bodies adjust to this drug.

For this pilot study, a convenience sample of 20 participants was chosen without formal power calculations. Should the results of this study suggest that niacin is tolerable, effective at reducing T-cell activation and/or has a positive effect on QoL, fatigue, depression and neurocognition, future studies will be performed. As a crossover study, two other comparisons will be made between the two arms: 1) the period of niacin plus ART in arm 1 will be compared to niacin plus ART in arm 2; 2) the period of ART alone in arm 1 will be compared to ART alone in arm 2. This will allow for the further evaluation of the potential continuity of the hypothesised effect of niacin following its discontinuation. The data obtained in this pilot study should be sufficient to assist in formal power calculations for such future studies.

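### With no washout, measuring each period from its own start counts any rebound off niacin in arm 1 as a control change, so a pooled estimate is 1.0 to 1.5 times the true effect and the similarity check is misread as a sign of carryover

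*Protocol article*

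**What the plan says.** The Sample size and statistical analyses section of the Protocol article defines the niacin periods as "from week 0 to week 24 of arm 1, and from week 24 to week 48 of arm 2", and sets them against "the control periods of ART alone (from week 24 to 48 of arm 1, and from week 0 to 24 of arm 2". The between-group t-test in each period and the paired t-test within each treatment order are both stated on change over the period.

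The two periods abut. The Randomization section describes "arm 1: ER niacin supplementation for 24 weeks followed by 24 weeks of ART alone", the Figure 1 legend says "Arm 1: ER niacin administration begins at week 0 and ends at week 24", and a footnote to Table 3 says "Participants will end ER niacin administration at the end of week 24". The marker has only three time points: "Levels of T-cell activation will be assessed in blood samples on weeks 0, 24 and 48". Arm 1's last on-niacin sample is therefore also the starting value of its control period.

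The Background says of the expected fall in activation that "such a decrease may reverse after ER niacin is discontinued".

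The analysis section then sets a switch. If the two period effects look clearly different, which it says carryover may cause, attention moves to the comparison of arms at week 24. If they look similar, the two within-order paired comparisons are combined. The same approach covers the secondary outcomes. The Discussion adds a comparison of the ART-alone periods between arms, and says of the added comparisons: "This will allow for the further evaluation of the potential continuity of the hypothesised effect of niacin following its discontinuation".

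**The concern.** A control change should show what happens to the marker without niacin. In arm 2 (weeks 0 to 24) it does. In arm 1 (weeks 24 to 48) it shows what happens when niacin is withdrawn. If the effect wears off, that change is a rise. Subtracting it from the fall on niacin counts part of the same effect twice.

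Two things are at stake. First, the article says the pilot should assist power calculations for later studies, so an inflated effect would be passed on. Second, the switch between the pooled and week-24 analyses treats dissimilar periods as a mark of carryover. On change scores, dissimilarity arises when the effect has gone, which is when a crossover is valid.

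**Working it through.** **The plan's own figure.** For 20 pairs, 80% power and two-sided 5%, the detectable ratio of difference to SD of differences is (1.960 + 0.842)/√20 = 0.626. Power at 0.625 is 79.8% by the normal approximation. The stated 0.625 reproduces. It says nothing about what the difference estimates, which is the issue here.

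**Inputs.** The period definitions, the absence of a washout and the three sampling times come from the sections cited above. Two symbols are needed: d, the fall caused by niacin, and c, the fraction of that fall still present in arm 1 at week 48. The documents do not give c, so the range 0 to 1 is shown.

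**Expected levels relative to week 0, at weeks 0, 24 and 48.**
- Arm 1: 0, -d, -cd
- Arm 2: 0, 0, -d

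**Contrasts on change.**
- Period 1: (-d) - 0 = -d
- Period 2: (-d) - (-cd + d) = -(2-c)d
- Paired within arm 1: (-d) - (-cd + d) = -(2-c)d
- Paired within arm 2: (-d) - 0 = -d
- Pooled, equal weight: -(3-c)d/2

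A time trend common to both arms cancels from the period contrasts and from the equal-weight average.

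**Contrast on end-of-period values.** Arm 1 gives -d - (-cd) = -(1-c)d and arm 2 gives -d, so the average is -(2-c)d/2.

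| c | Period 1 | Period 2 | Pooled changes | Pooled end-of-period values |
|---|---|---|---|---|
| 0 | 1.00d | 2.00d | 1.50d | 1.00d |
| 0.5 | 1.00d | 1.50d | 1.25d | 0.75d |
| 1 | 1.00d | 1.00d | 1.00d | 0.50d |

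For scale, take the 50% fall that the Discussion expects and assume full reversal. Period 1 then shows a fall of 50% of baseline, period 2 shows 100%, and the pooled figure is 75%.

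**The similarity check.** Period 2 minus period 1 is -(1-c)d. This is zero when the effect fully persists and largest (d against 2d) when none persists. In simulation with 10 per arm and dissimilarity judged by a 5% test, full persistence was flagged in 5% of trials, the nominal rate. Full reversal was flagged in 63% of trials if the true ratio is 0.625, and in 34% if it is 0.417.

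**Averaged over the switch.** These figures assume d = 1 within-person SD, c = 0, between- and within-person SD both 1, and 10 per arm. With dissimilarity judged at the 20%, 10% or 5% level, the reported estimate averages 1.08d, 1.15d or 1.23d. That average mixes two groups of trials. Those that pool still average 1.50d. Those sent to week 24 average about 0.67d to 0.81d, because they are selected for a small period 1 effect relative to period 2.

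**Precision and error rate, same assumptions.** The paired difference of changes is twice the week-24 value minus the week-0 and week-48 values, with SD √(4+1+1) = 2.45 within-person SDs. For end-of-period values it is √2 = 1.41. Power at c = 0 is 85% with end-of-period values, 74% with changes always pooled, and 42% to 49% with changes plus the switch at the 20% or 10% level. With d = 0 the type I error is about 5% to 6%, with or without the switch.

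**The case against.** The strongest reply is that the plan does not always pool. When reversal is full the period effects are d and 2d, so the switch often moves to week 24, and the average inflation is nearer 1.1 to 1.2 than 1.5. With d = 2 within-person SDs it is only 1.01 to 1.04. On change scores the switch also leans the right way for bias: it discourages pooling when the pooled figure is inflated and permits it when the figure equals d. This stands, and it rules out describing the inflation as 1.5 without the condition that the trial pools. It is not a safeguard, because neither of the two possible estimates is centred on d once it has been selected, and the document sets no threshold for dissimilarity.

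Several stronger readings are tempting, and the documents do not support them:
- A reader might infer that the protocol predicts full reversal. The Background says only that the decrease may reverse and gives no extent.
- A reader might infer that a later trial sized on the pooled figure would be far too small. That raises the mean and leaves the SD alone. Under the assumptions above the standardised effects are 1.5/2.45 = 0.61 for changes and 1/1.41 = 0.71 for end-of-period values, so sizing on the pilot's pooled mean with its own SD would ask for more patients, by (0.71/0.61)² or about 1.33 times. The harm is an effect size that is wrong on its own scale.
- A reader might infer that the Discussion's ART-alone comparison is inverted. It names no metric. On changes it estimates (1-c)d, and zero after a clear period 1 effect can fairly be read as no rebound.

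One phrase in the analysis section, about control time-points, could hint at levels. The primary comparison and every named test are nevertheless on change.

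**Conclusion.** The concern holds in this form. As defined, arm 1's control change absorbs any reversal of the niacin effect. Whenever the trial pools, the estimate is (3-c)d/2, between 1.0d and 1.5d. This is algebra from the stated definitions and needs only that c lies between 0 and 1. A rebound above baseline would take it beyond 1.5d.

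The similarity check cannot serve as evidence about carryover: it tends to discard period 2 when the crossover is valid, and it cannot detect full persistence. The averaged inflation, the selection effect and the power figures rest on assumed values of d and the SDs and on assumed thresholds, none of which the documents give. The test of whether there is any effect is nearly unharmed. The damage is to the size of the estimate and the reading of carryover, for the primary outcome and for every secondary outcome analysed the same way.

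**What to change.** 1. Compare end-of-period values at weeks 24 and 48, adjusted for the week-0 value, in one linear mixed model with treatment and period as fixed effects and participant as random.
2. Always report the randomised week-24 comparison beside it, and remove the switch on apparent dissimilarity.
3. Judge persistence from arm 1's week-48 value against its own week-0 value, set against arm 2's week-0 to week-24 change to allow for time trend (which covers only half of that interval). If ART-alone changes are compared between arms, describe the result as a measure of reversal.
4. State that the week-24 effect will be used to size later studies.

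The cost is wording; the same three samples suffice. The drawback is that if the effect persists the end-of-period estimate is diluted, to 0.75d at c = 0.5 and 0.5d at c = 1. That error is conservative, and the week-24 estimate, reported in every case, stays unbiased.

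### The choice between the pooled crossover test and the week-24 comparison is made after seeing both period effects, which modestly inflates the 5% level and misreads carryover

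*Protocol article*

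**What the plan says.** All of this is in the protocol article, mainly under Sample size and statistical analyses. The primary comparison sets the change during niacin plus ART against the change during ART alone. Each period is first tested between arms with a t-test on change. What follows depends on the result:

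- "If the treatment effects in the two time periods look distinctly dissimilar, which may occur due to carryover effects of treatment", the focus moves to arm 1 against arm 2 at the end of 24 weeks.
- "If the results of these comparisons in the two treatment periods are similar, then within each treatment order, a paired t-test will be used", and the two within-order results are pooled.

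The section gives no criterion for similar or dissimilar. It applies the same approach to the secondary outcomes and states: "All statistical tests performed will be two-tailed with significance determined by reference to the 5% level". On size, "a convenience sample of 20 participants was chosen without formal power calculations", and "The primary comparison would be based on 20 pairs of observations", with a ratio of 0.625 quoted for 80% power.

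Two other places matter. T-cell activation in blood gives measurements at weeks 0, 24 and 48 only, and Figure 1 and Table 2 start niacin in arm 2 straight after the week-24 visit. Week 24 therefore ends period 1 and is the baseline of period 2, with no washout. The Background expects that the fall in activation may reverse once niacin stops.

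**The concern.** This is a two-stage crossover procedure: a preliminary look at the difference between period effects decides which test is reported. That difference is built partly from the week-24 estimate, so the week-24 test tends to be chosen when its own estimate is extreme. The claimed 5% level then does not hold exactly. The pilot's estimates are also meant to help size later trials, so a selectively reported estimate would be carried forward. Because the gate is applied outcome by outcome, different outcomes can end up under different tests with different power. Finally, the gate is justified as protection against carryover, so it matters whether it responds to carryover at all.

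**Working it through.** **1. The plan's own figure.** Inputs: two-sided 5%, 80% power, 20 pairs. Normal approximation: (1.960 + 0.842)/√20 = 0.626, so 0.625 reproduces (power 79.8%). A paired t-test with 19 df has 75.5% power at 0.625 and needs 0.660 for 80%. The figure belongs to the pooled branch. For the week-24 branch (10 against 10), take the same true effect with no reversal and convert it to SDs of change:

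- independent visit errors: 0.625 × √6/√2 = 1.083, power about 63%;
- independent changes: 0.625 × √2 = 0.884, power about 46%.

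**2. Why the gate is not neutral.** Let D1 and D2 be arm 1 minus arm 2 mean changes in periods 1 and 2. The period effects are D1 and −D2, so the gate looks at D1 + D2. With 10 per arm:

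- Independent visit errors (unit variance): Var D1 = Var D2 = 0.4, Cov(D1, D2) = −0.2, Var(D1 + D2) = 0.4, Cov(D1, D1 + D2) = 0.2. Correlation 0.2/0.4 = 0.5.
- Independent changes (unit variance): Var D1 = 0.2, Var(D1 + D2) = 0.4, Cov(D1, D1 + D2) = 0.2. Correlation 0.2/√(0.2 × 0.4) = 0.71.

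The pooled estimate (D1 − D2)/2 is uncorrelated with D1 + D2, because Var D1 = Var D2. So the pooled test keeps its level when no switch occurs, and the week-24 test does not keep its level when one does.

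**3. Size under the null.** 400,000 simulated trials, 10 per arm, no treatment, period or carryover effect, no dropout, each test at two-sided 5%. The article gives neither a trigger nor a correlation, so both were assumed and varied. Either test fixed in advance rejects in 5.0%.

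| Trigger for switching | Independent visit errors: overall / week-24 test given switch | Independent changes: overall / week-24 test given switch |
|---|---|---|
| p<0.05 | 5.6% / 16.9% | 6.4% / 31.9% |
| p<0.10 | 5.9% / 13.8% | 6.9% / 23.9% |
| p<0.20 | 6.2% / 10.7% | 7.4% / 16.6% |
| p<0.30 | 6.2% / 9.0% | 7.4% / 12.9% |
| p<0.50 | 6.1% / 7.1% | 7.0% / 8.9% |
| one period significant, other not | 5.7% | 6.9% |
| opposite signs | 5.5% | 7.3% |

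As a check at p<0.10 with visit errors: 0.100 × 13.8% + 0.900 × 5.0% = 5.9%. If whichever test is significant is reported, the ceiling is 7.4% to 8.5%.

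**4. What the gate sees under carryover.** Let niacin lower the marker by d.

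| | Arm 1 change, period 1 / 2 | Arm 2 change, period 1 / 2 | Period effects | Pooled change score |
|---|---|---|---|---|
| Full reversal off drug | −d / +d | 0 / −d | d and 2d | (2d + d)/2 = 1.5d |
| Full persistence | −d / 0 | 0 / −d | d and d | (d + d)/2 = d |

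With d equal to one assumed SD unit and a p<0.10 trigger, the switch occurs in 45% of trials under full reversal and in 10%, the chance rate, under full persistence.

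**5. Estimate after a switch.** At the same trigger, with independent visit errors, the mean week-24 estimate among switched trials is about 0.00 for a true 0 and 1.00 to 1.01 for a true 1 when both period effects are equal. Under full reversal it is 0.73 to 0.74 for a true 1.00. In that scenario the gate also lowers the overall rejection rate from 74% (pooled test always used) to 49%.

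**The case against.** The strongest defence is that the damage is small and the setting forgiving. The overall excess is roughly 0.5 to 2.5 percentage points, the study is a proof-of-concept with a convenience sample, and an unseen SAP might supply a numeric trigger. The first two points stand and limit the severity. The third does not help, because every numeric cut-off tried still exceeds 5%. The weakness is the gate itself.

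Four stronger readings are tempting and are not supported:

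- *The 5% level collapses.* The 14% to 24% figures apply only to trials that switch, about one in ten at p<0.10 under the null.
- *The primary test is undefined.* Both tests are named. What is open is the rule for choosing between them, so which one is primary is not known in advance.
- *Open-label conduct causes the inflation.* It does not. Period effects must be unblinded to be compared in any trial, and the endpoint is a flow-cytometry percentage.
- *Any estimate after a switch is biased.* When the true period effects are equal, selection on the size of their difference is symmetric and leaves the mean unchanged. Bias needs truly different period effects, which is what reversal off drug produces on change scores.

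**Conclusion.** The point holds at moderate size. Choosing the analysis after inspecting the period effects takes the nominal two-sided 5% to about 5.5% to 7.5% overall, with a ceiling near 8.5% if the significant test is the one reported. It biases the estimate after a switch when the period effects truly differ. The more specific fault is that the gate does not do its stated job: on change scores with no washout it tends to fire when the effect reverses, which the Background anticipates, and stays at its chance rate when the effect fully persists.

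The error rates rest on 10 per arm, no dropout, assumed triggers and two assumed correlation structures. The week-24 comparison is taken to be on change from week 0, as in the section's t-tests. The d and 2d result needs only the planned change scores and the absence of washout. Severity: should be fixed, given that the trial is a proof-of-concept study which nevertheless claims 5% testing.

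**What to change.** Delete the similarity gate and name one primary analysis in advance, the same for all outcomes. Either choice is defensible:

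- **The randomised week 0 to 24 between-arm comparison of change.** It is free of carryover. Its cost is power: about 46% to 63% at the effect for which the plan quotes 80%, so the 20-pair statement would need to be replaced.
- **One period-adjusted crossover analysis.** Base it on end-of-period values (weeks 24 and 48) with a period term and week-0 adjustment, not on pooled change scores, which average 1.5d under full reversal. End-of-period values give d in both periods under full reversal. Under full persistence they give d and then 0, so the estimate is diluted to (d + 0)/2 = d/2.

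Always report the analysis not chosen as a fixed sensitivity analysis, with no preliminary carryover test. Persistence can be described through the comparison of the two ART-alone periods already planned in the Discussion. No new visits or samples are needed. The first option is mainly a change of wording. The second also changes the analysed quantity from changes to end-of-period values and should be declared as such.
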